#### 2.3.2. Diagnostic Criteria for CKD

CKD is characterized by structural or functional abnormalities in the kidney, and the complex symptom situation lasts for more than 3 months, impacting health well-being [37]. KDIGO classification of CKD is as follows (Table 2).

#### 2.3.3. Diagnostic Criteria for TCM Syndrome Differentiation

According to Guidelines for Clinical Research of Chinese Medicine (New Drug) [38] and Diagnosis, Syndrome Differentiation, and Efficacy Evaluation of Chronic Renal Failure (Trial Protocol) [39], patients conformed to 4 primary symptoms and 1–2 secondary symptoms listed below can be diagnosed with spleen-kidney qi deficiency and toxicity stasis inter-combination syndrome. The primary symptoms are as follows: (1) fatigue or shortness of breath and reluctance to speak; (2) nausea and vomiting; (3) dim complexion; and (4) soreness in waists and knees. The secondary symptoms are as follows: (1) abdominal fullness and distention; (2) lack of appetite and numb to react; (3) squamous and dry skin; (4) thick and greasy tongue coating; (5) dark and purple tongue or petechiae; and (6) fine tart or slow sunken pulse.

#### 2.3.4. Inclusion Criteria

Participants will be enrolled in the trial if they satisfy all the following criteria: (1) meet the diagnostic criteria for CKD stages 2–4 and AKI grades 1–2; (2) meet the diagnostic criteria of TCM syndrome differentiation; (3) 24 h U-pro ≤2.5 g; (4) between 18 and 70 years old; and (5) voluntary to be enrolled in the clinical trial and sign informed consents.

#### 2.3.5. Exclusion Criteria

Participants will not be enrolled in the trial if they have any of the following criteria: (1) pregnancy or lactation; (2) with serious primary diseases of other organs in urgent need of immediate treatment or with malignant tumors, active tuberculosis, and other consumption diseases; (3) with anorectal diseases not suitable for enema; (4) kidney transplantation; (5) psychopaths, patients who cannot cooperate; (6) allergic to therapeutic medicine; and (7) participating in clinical trials or participated in other clinical trials within 3 months.

#### 2.3.6. Withdrawal Criteria

Participants will withdraw from the trial if (1) poor subject compliance; (2) allergic to therapeutic medicine; (3) cases lost to follow-up in the trial; (4) patients request to withdraw from the trial; (5) cannot meet the inclusion criteria after inclusion; and (6) serious diseases or complications occur suddenly during the trial that has no causal relationship with AKI. Participants developing serious diseases or complications during the treatment cannot be withdrawn until the assessment of causal relationship with AKI has been accomplished. Complications such as cardiorenal syndrome and sepsis usually indicate the progression of AKI and should not be simply excluded from the efficacy analysis. Reasons should be given for withdrawal cases, and related forms should be reserved for future reference. Those cases are not statistically analyzed for efficacy, but adverse reactions should be analyzed for those who have received at least one treatment and can be determined to have records of adverse reactions. Participants who withdraw within two weeks after treatment will be defined as missing case and will not be enrolled in the pee-protocol population.

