## 1. Introduction

AKI is defined as an abrupt decrease in kidney function, which encompasses both structural damage and functional loss [1]. According to 2012 Kidney Disease Improving Global Outcomes (KDIGO-2012) AKI definition [2], it is diagnosed by an increase in Scr to at least 0.3 mg/dl (26.5 *μ*mol/l) within 48 hours, or an increase in Scr to more than 1.5 times baseline during prior 7 days, or a urine volume decrease to less than 0.5 ml/kg/h for 6 hours. AKI is a global public health challenge [3], it is a severe complication caused by various critical diseases leading to considerable morbidity and mortality both in short term and long term [4, 5], and it implicates a great burden in sanitary costs [6]. A on C accounts for about a third of total AKI [7]. It is estimated that there are more than 13 million patients with AKI worldwide every year [8]. US statistical data indicate that the incidence of AKI is about 2100 per million [9]. A study on the clinical status of AKI in China points out that over 2 million patients are hospitalized with AKI, and about 700,000 patients died of AKI every year [10].

For severe AKI (grade 3), RRT should be implemented as soon as possible. It is reported that about 26.9% of patients with AKI require RRT eventually [11]. Current modalities of RRT for AKI include intermittent hemodialysis (IHD), continuous renal replacement therapy (CRRT), and peritoneal dialysis (PD). Also, sustained low-efficiency dialysis (SLED) has been put forward as an alternative RRT method and applied to clinical practice in many medical institutions worldwide [2, 12]. Recently, although AKI has attracted more and more attention and lots of related basic or clinical studies have been accomplished, there is still a lack of recognized drug treatment method for AKI grades 1–2 [13–15].

Studies have confirmed that oxidative stress injuries exist in the occurrence of AKI, and it plays an important role in affecting the prognosis of AKI [16]. At the same time, oxidative stress might induce inflammation by activating macrophages and complement systems, which would aggravate the potential kidney damage [16, 17]. Therefore, it is of great significance to pay more attention to the effect of oxidative stress in AKI.

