### 2.5. Interventions

Patients diagnosed with CKD stages 2–4 complicated with AKI grades 1–2 will be enrolled after signing written informed consents. They will be randomly divided into the RG group, the CHF group, and the RG + CHF group. To minimize potential loss and help participants conduct the trial smoothly, three group patients will receive study behavior and health education, and they will also be told possible risks and benefits, their rights and obligations, and how to handle an emergency situation. All patients will receive a low-salt, high-quality, and low-protein diet (protein intake 0.6–0.8 g/kg/d). Also, they will receive general treatments, whose purposes are to correct water, electrolyte, and acid-base balance disorders, control blood pressure, improve anemia, and correct renal bone diseases. Designed investigations will keep in touch with participants regularly and assist them to receive treatment and testing on schedule.

The RG group will be given RG 1.8 g added to 0.9% normal saline or 5% glucose 250 ml for injection, intravenous injection (IV), once per day for 2 weeks. The CHF group will be given CHF orally, twice per day for 2 weeks. At the same time, the concentrated solution of CHF will be given an enema, once per day for 5 days, and then rest for 2 days, 5 times in a week. The RG + CHF group will be the combination of the RG group and the CHF group, and intervention methods are the same as the above.

Pharmaceutical compositions of CHF are mainly as follows: prepared rhubarb (Zhida Huang), Ligusticum wallichii (Chuan Xiong), Codonopsis pilosula (Dangshen), Coptidis rhizome (Huanglian), Smilacis glabrae (Tufuling), etc. RG will be produced by Chongqing Yaoyou Pharmaceutical Co. Ltd., and CHF will be produced by Jiangyin Tianjiang Pharmaceutical Co. Ltd. Therefore, the quantity and quality of medicine can be effectively guaranteed.

Related examinations will be conducted and collected at baseline, every 1 week during treatment. Patient information will be recorded, and efficacy-related examinations, mechanism-related indicators, safety-related indicators, and drug management will be closely observed. Measured items and time points are listed in Table 3.

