### 2.6. Outcome Measures

The primary evaluation outcome will be the change in the slope of Scr over 2 weeks. Posttreatment changes in BUN, eGFR, and urinary AKI biomarkers including urinary NGAL, IL-18, *γ*-GT, and TCM symptoms will be the secondary evaluation outcomes.

In addition to the secondary evaluation outcome, inflammatory indicators including TNF-*α* and IL-6 and oxidative stress indicators including heme oxygenase-1 (HO-1), malondialdehyde (MDA), and superoxide dismutase (SOD) will also be measured before and after treatment.

Safety outcomes and vital sign indicators (electrocardiogram, blood routine, urine routine, serum potassium, hemoglobin, etc.) will be recorded once before and 2 weeks after medication. Meanwhile, AEs will be closely observed, meticulously recorded, and properly handled by investigators throughout the study.

HCG: human chorionic gonadotropin; Scr: serum creatinine; BUN: blood urea nitrogen; eGFR: estimated glomerular filtration rate; TCM: traditional Chinese medicine; NGAL: neutrophil gelatinase-associated lipocalin: IL-18: interleukin-18; *γ*-GT: gamma-glutamyl transpeptidase; IL-6: interleukin-6; TNF-*α*: tumor necrosis factor-*α*; HO-1: heme oxygenase-1; MDA: malondialdehyde; SOD: superoxide dismutase.

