## Figures and Tables

**Figure 1 fig1:**
[figure not shown]
Flow chart of the study. RG: reduced glutathione, CHF: Chuan Huang Fang.

**Table 1 tab1:** KDIGO classification of AKI.

Stage	Serum creatinine	Urine output
1	1.5–1.9 times baseline, or ≥0.3 mg/dl (26.5 *μ*mol/l) increase	<0.5 ml/kg/h for 6–12 h
2	2.0–2.9 times baseline	<0.5 ml/kg/h for≥12 h
3	3.0 times baseline, or≥4.0 mg/dl (353.6 *μ*mol/l), or initiation of RRT, or < 18 years, eGFR <35 ml/min per1.73 m^2^	<0.3 ml/kg/h for≥24 h or anuria for ≥12 hours

**Table 2 tab2:** KDIGO classification of CKD.

GFR category	GFR (ml/min/1.73 m^2^)	Terms
**G1**	≥90	Normal or high
**G2**	60–89	Mildly decreased
**G3a**	45–59	Mildly to moderately decreased
**G3b**	30–44	Moderately to severely decreased
**G4**	15–29	Severely decreased
**G5**	<15	Kidney failure

**Table 3 tab3:** SPIRIT table: measured items and time points.

Items	Baseline	Treatment	
	0 week	1 week	2 weeks
General	×		
**Informed consent**	×		
**Inclusion and exclusion criteria**	×		
**General information**	×		
**General physical examination**	×		
**Urine HCG (only women)**	×		
**Medical and drug use history**	×		
**Concomitant disease and treatment**	×		
**Combined medication**	×	×	×
Randomization	×		
Intervention			

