**RG group**			
**CHF group**			
**RG** **+** **CHF group**			
Effectiveness observation			
**Renal functions (Scr, BUN, eGFR)**	×		×
**AKI biomarkers (NGAL, IL-18, *γ*-GT)**	×		×
**TCM symptoms**	×		×
Mechanism observation			
**Inflammatory indicators (IL-6, TNF-*α*)**	×		×
**Oxidative stress indicators (HO-1, MDA, SOD)**	×		×
Safety observation			
**Electrocardiogram**	×		×
**Blood routine**	×		×
**Urine routine**	×		×
**Fecal routine and occult blood test**	×		×
**Serum potassium**	×		×
**Hemoglobin**	×		×
**Adverse events**		×	×
Drug management			
**Drug distribution**	×	×	×
**Drug recycling**		×	×
**Drug count**		×	×
Research conclusion			×

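### AKI-progression cases are kept in a creatinine-only efficacy analysis with no rule for creatinine after dialysis, and no efficacy outcome counts grade 3, RRT or death

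*Protocol article*

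**What the plan says.** All references are to the protocol article.

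- **Who leaves.** Section 2.3.6 withdraws a patient for a complication only when "serious diseases or complications occur suddenly during the trial that has no causal relationship with AKI". It then adds: "Complications such as cardiorenal syndrome and sepsis usually indicate the progression of AKI and should not be simply excluded from the efficacy analysis". Of withdrawn patients it says: "Those cases are not statistically analyzed for efficacy". Criterion 5 of the same list also withdraws patients who turn out, after entry, not to satisfy the inclusion criteria.
- **A second exit.** Section 2.3.7 lets a patient stop because of severe complications and asks for an intention-to-treat analysis of such cases.
- **Primary outcome.** Section 2.6: "The primary evaluation outcome will be the change in the slope of Scr over 2 weeks". The secondary outcomes there are BUN, eGFR, urinary biomarkers and TCM symptoms. Progression, RRT and death are not among them.
- **When Scr is measured.** Table 3 marks renal function at baseline and week 2 only. Section 2.5 reads differently: "Related examinations will be conducted and collected at baseline, every 1 week during treatment".
- **Grade 3 and RRT.** Table 1 defines grade 3 by "3.0 times baseline, or≥4.0 mg/dl (353.6 *μ*mol/l), or initiation of RRT", among other criteria. The Introduction says grade 3 calls for RRT and cites 26.9% of all AKI patients as needing it eventually.
- **Analysis.** Section 2.10 uses the full analysis set and a repeated-measures ANOVA on Scr, and says there will be no additional analyses.

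**The concern.** Keeping progressing patients in the efficacy analysis is the right instinct, because they are the failures the treatment is meant to prevent. But once dialysis starts, Scr partly measures dialysis clearance and no longer tracks kidney recovery. If such a value is used unadjusted, the patient with one of the worst courses contributes a smaller rise than the kidney would have shown, or even a fall. A patient who dies before week 2 contributes no follow-up value on the Table 3 schedule.

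The bias can go either way. More dialysis in the comparator arms would lower their week-2 means and hide a real benefit of the combination. More dialysis in the combination arm would lower its mean and make it look better. Section 2.4 concedes that treatment is open, so decisions to start RRT could differ by arm, and masking the laboratory staff does not prevent that. With no count of progression, RRT or death among the efficacy outcomes, nothing beside the Scr result would show that this had happened.

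**Working it through.** **Step 1: what can happen to a patient who progresses to grade 3**

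| Route | Basis | Effect on the primary analysis |
|---|---|---|
| Kept, dialysed, week-2 Scr measured | 2.3.6 retention sentence, full analysis set in 2.10 | No rule prevents the dialysis-altered value from being used |
| Withdrawn under criterion 5, if grade 3 is read as no longer meeting entry criteria | 2.3.6 | Left out of efficacy |
| Stops for severe complications | 2.3.7 | Intention-to-treat is asked for, but no value is specified |
| Dies before week 2 | Table 3 | No week-2 value |

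On none of these routes is progression counted as a failure. A week-1 Scr, if section 2.5 rather than Table 3 is followed, would not change that.

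**Step 2: analysed number per arm**

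Section 2.9 gives SD 44.43 µmol/l, difference 30 µmol/l, power 0.90, α 0.05, 20% dropout and 54 per arm. A three-group one-way ANOVA F-test with means 160.39, 160.39 and 130.39 needs 43 per arm (power 0.903). Then 43 / (1 − 0.20) = 53.75, rounded up to 54, which matches the plan. (The one-sided two-group calculation that section 2.9 describes gives 38, then 48 after dropout. That is a separate matter.) So 43 is taken as the analysed number.

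**Step 3: size of the distortion**

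Let k be the excess number of dialysed patients in one arm over another, and g the amount by which dialysis lowers each one's week-2 Scr. The difference in mean change over 2 weeks shifts by

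shift = k × g / 43.

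The documents give neither k nor g, so both are assumptions.

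| k | g = 50 | g = 100 | g = 200 |
|---|---|---|---|
| 1 | 1.2 | 2.3 | 4.7 |
| 3 | 3.5 | 7.0 | 14.0 |
| 6 | 7.0 | 14.0 | 27.9 |

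For example, 3 × 100 / 43 = 7.0 and 3 × 200 / 43 = 14.0 µmol/l. If all 54 per arm are analysed, the same two cases give 3 × 100 / 54 = 5.6 and 3 × 200 / 54 = 11.1.

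**Step 4: against the planned effect**

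A shift as large as the planned 30 µmol/l needs k × g = 30 × 43 = 1,290. That is 12.9 excess patients at g = 100, or 6.45 at g = 200. A shift of 7.0 is 7.0 / 30 = 23% of the planned effect, and 14.0 is 47%. If dialysis is equally frequent and equally effective in all arms, k = 0 and the shift disappears from the difference in means, although each arm's mean is still altered.

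**The case against.** A reader might infer that the plan scores dialysed patients as improved. The documents do not say so. The retention sentence names cardiorenal syndrome and sepsis, not grade 3 or dialysis, and no section states that a post-dialysis Scr will be used. That possibility arises because nothing rules it out. A dialysed patient's Scr may also still lie above the entry value, in which case worsening is understated and no improvement is shown. This objection stands, and it limits the point to what could happen.

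It can also be said that handling of events such as RRT and death belongs in a full protocol or analysis plan that is not shown. That is partly right, since the detail may sit there. But the retention rule, the Scr-only endpoint and the list of efficacy outcomes are fixed here, section 2.10 closes the door on additional analyses, and an analysis plan cannot be presumed to supply an outcome that the protocol omits.

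Retention is not certain either, given criterion 5 and section 2.3.7. That is true, but those routes drop the patient or leave the handling unclear, so they do not rescue the analysis.

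Failures would not disappear altogether: section 2.12 treats death and life-threatening complications as serious adverse events and promises to publish them. This stands, but as safety reporting and not as an efficacy result.

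Lastly, the 26.9% concerns all AKI over an open period. It is not a rate for grades 1–2 over two weeks, and the entry criteria probably make the rate here lower. No size can be built on it.

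**Conclusion.** The point holds in a limited form. The plan keeps AKI-progression cases in an efficacy analysis that rests on Scr alone, gives no rule for Scr after RRT starts, and counts neither grade 3, RRT nor death as an efficacy outcome. A dialysis-lowered value could therefore be read as benefit, and a death leaves a gap. The stronger claim, that the worst outcome will be scored as improvement, is not supported.

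The size cannot be determined from the documents. Under the assumptions shown, one to three excess dialysed patients in an arm of 43, with Scr lowered by 100 to 200 µmol/l, shift the contrast by 2.3 to 14.0 µmol/l against a planned 30. Balanced rates would largely cancel. Reversing the planned effect would take more excess patients than this, so the likelier harm is a distorted estimate. The issue should be corrected but falls short of a must-fix, and confidence is moderate.

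**What to change.** 1. **Section 2.6:** add, as a secondary outcome, the proportion per arm with Table 1 grade 3, initiation of RRT, or death within 2 weeks.
2. **Section 2.10:** state that Scr taken after RRT starts is not analysed as a raw value, and say how those patients are represented in the planned ANOVA. Pre-specify a rank-based analysis of the Scr outcome in which RRT and death rank worst, at least as a sensitivity analysis beside the ANOVA, and amend the sentence that rules out additional analyses. The ANOVA and the mean-based sample size can then stay.
3. **Case report form:** record the RRT start date.
4. **Sections 2.3.6 and 2.3.7:** reconcile them, including criterion 5, on whether progressing patients stay in the efficacy analysis.

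Carrying forward the last Scr before RRT is not advised. On the Table 3 schedule that value may be the baseline, which would score a progressing patient as unchanged.

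The cost is wording changes, one more analysis and one form field, with no extra visits or patients. The downside is that a rank-based result is less simple to describe than a mean change. The change should be made before outcome data by arm are seen.

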#### 2.3.7. Shedding Criteria

Natural shedding and loss of follow-up during observation may occur during the trial. He/she will quit by himself/herself if it is not suitable to continue participating in the trial because of severe complications or unpredictable events. Shedding cases should be documented in detail, and intention-to-treat (ITT) analysis should be performed in the end.

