### 2.10. Statistical Analysis

The principal analysis will be conducted on a full analysis set (FAS), which consists of participants randomly allocated into two groups. Participants completing and complying well with the study protocol without major violation will be referred to the per-protocol population. All participants taking test drugs will be enrolled in safety analysis and conform with the ITT principle.

For non-normally distributed variables, mean ± standard deviation or median will be brought to describe continuous variables. Categorical variables will be presented in the form of numbers and percentages. The difference in Scr will be tested using the one-way ANOVA with repeated measures. The secondary outcomes will be compared between two groups using the independent-samples Student's *t*-tests for normally distributed continuous data and using Pearson's chi-square test (or Fisher's exact test if cell count <5 in any cell) for categorical data. Two-sided tests will be used for all statistical tests, and *P* < 0.05 will be considered statistically significant. SPSS (version 21.0) software will be used to carry out statistical analysis by a biostatistician not involved in the study. No additional analyses or interim analysis will be performed.

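### Section 2.3.6 excludes withdrawn participants from the efficacy analysis without limiting this to the per-protocol set, contradicting the ITT and FAS rules in Sections 2.3.7 and 2.10

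*Protocol article*

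**What the plan says.** Section 2.3.6 gives six grounds for withdrawal: poor compliance, allergy to study medicine, loss to follow-up, patient request, a fifth worded "cannot meet the inclusion criteria after inclusion", and sudden serious disease with no causal link to AKI. Of withdrawn participants it says "Those cases are not statistically analyzed for efficacy". One protection comes just before: complications such as sepsis or cardiorenal syndrome usually signal AKI progression and are not simply to be left out of the efficacy analysis. A separate later sentence keeps participants who withdraw within two weeks out of the per-protocol population.

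Section 2.3.7, on dropouts and loss to follow-up, says "intention-to-treat (ITT) analysis should be performed in the end".

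Section 2.10 says "The principal analysis will be conducted on a full analysis set (FAS" and defines that set by random allocation. It defines the per-protocol population separately and puts everyone who took test drug in the safety analysis.

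On safety, Section 2.3.6 asks for adverse reactions to be analysed in withdrawn participants who had at least one treatment and who "can be determined to have records of adverse reactions".

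**The concern.** The sections disagree on who enters the primary analysis. A participant lost to follow-up is excluded from efficacy under Section 2.3.6, but retained under Sections 2.3.7 and 2.10.

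The choice matters because the listed grounds arise after randomisation and can depend on treatment. Section 2.4 says treatment cannot be blinded. Section 2.5 gives one arm a daily infusion, another an oral preparation plus enemas, and the third all of these. Compliance, allergy and requests to leave may therefore differ by arm. The article gives no threshold for poor compliance, so that ground may be applied by someone who knows the allocation. If the participants removed are doing worse than those kept, the arm that loses more of them looks better than it is. If they are doing better, the error runs the other way. With two conflicting rules in the protocol, the choice between them could also be made after the data are seen.

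**Working it through.** **The passages side by side**

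| Case | Section 2.3.6 | Section 2.3.7 | Section 2.10 (FAS) |
|---|---|---|---|
| Lost to follow-up | Out of efficacy | ITT | In |
| Poor compliance, allergy, patient request | Out of efficacy | Not named individually | In |
| Complication judged to be AKI progression | Not simply excluded | ITT if the participant drops out | In |

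Reading the Section 2.3.6 sentence as a per-protocol rule does not work. It carries no such qualifier, and the per-protocol exclusion is stated on its own afterwards.

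**How many participants are affected**

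Inputs from Section 2.9: SD 44.43 μmol/l, target difference 30 μmol/l, α 0.05, power 0.90, 20% loss, 54 per group, 162 in total.

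The planned size can be reproduced if the calculation was an overall three-group F test (the article does not name the test). With group means 0, 0 and −30, the squared deviations from their mean sum to 100 + 100 + 400 = 600. The noncentrality is n × 600/44.43². At n = 43 it is 13.07 and power is 90.3%. Then 43/(1 − 0.20) = 53.75, which rounds up to 54 per group, or 162.

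At the planned loss, Section 2.3.6 would leave about 43 of 54 per group (129 of 162) for efficacy; the FAS holds all 162. Power for the F test is 90.3% with 43 analysed per group and 95.8% with 54. The loss allowance therefore largely protects power, and the issue is bias.

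**How large the bias could be**

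Assumptions not in the documents: creatinine is normal with SD σ = 44.43; a fraction p of an arm is lost, namely those above the (1 − p) quantile z of a latent variable correlated ρ with creatinine. The mean of those retained is then below the full-arm mean by

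ρ × σ × φ(z)/(1 − p).

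- p = 0.20: φ(0.842)/0.80 = 0.350, and 0.350 × 44.43 = 15.55. At ρ = 0.3 to 0.5 the shift is 4.7 to 7.8 μmol/l.
- p = 0.10: φ(1.282)/0.90 = 0.195, and 0.195 × 44.43 = 8.66. The shift is 2.6 to 4.3 μmol/l.
- Difference between arms, 20% versus 10%: ρ × (15.55 − 8.66) = ρ × 6.89, so 2.1 to 3.4 μmol/l. Divided by 30, that is 7 to 11%.
- Same p and same ρ in both arms: 0.

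A simpler check: if withdrawn participants are worse than those retained by D in both arms, the difference shifts by (p₁ − p₂) × D. For 20% versus 10% and D from 15 to 44.43 μmol/l this gives 1.5 to 4.4 μmol/l. For 30% versus 10% it gives 3.0 to 8.9 μmol/l.

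**The case against.** The best defence is that Section 2.10 already names the FAS as principal, so Section 2.3.6 is a stray sentence. That makes the repair easy but does not remove the contradiction, because the sentence is unqualified and concerns efficacy directly.

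The defence does succeed against several stronger readings that a reader might infer:

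- **That every withdrawal is dropped, including the worst renal outcomes.** The protection for AKI-related complications says otherwise. Section 2.3.6 also bars withdrawal for serious disease until its causal relation to AKI has been assessed.
- **That reason (5) removes patients who progress to AKI grade 3.** Taken that literally, it would also remove patients whose AKI resolves, since they too would no longer have grades 1–2. Table 3 checks eligibility at baseline only. The natural meaning is ineligibility discovered after enrolment, although the wording is loose.
- **That the FAS collapses to completers and that sensitivity analyses are forbidden.** The article does not say how missing values are treated within the FAS; a SAP may cover that. The sentence "No additional analyses or interim analysis will be performed" may refer to subgroup or adjusted analyses, and the same section itself defines a second population.
- **That the bias is 4.7 to 7.8 μmol/l, or 16 to 26% of the target.** That is the shift in one arm's mean. It becomes the bias in the comparison only if the other arm has no informative loss.
- **That adverse-event rates will have the wrong denominator.** Section 2.10 includes everyone who took test drug. The Section 2.3.6 wording defines no safety set; it is awkward and needs aligning.

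**Conclusion.** The contradiction is real and concerns the population for the primary comparison. As written, Section 2.3.6 makes post-randomisation exclusions, possibly related to treatment, in an open trial whose arms differ in burden. It can bias the comparison; the documents do not show that it will, nor in which direction. The illustrative 2.1 to 3.4 μmol/l rests on an assumed 20% versus 10% loss and an assumed correlation of 0.3 to 0.5. It falls to zero with equal informative loss and rises if loss is more unequal. The conclusion does not depend on that figure: the three sections must be reconciled before the data are analysed.

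**What to change.** 1. In Section 2.3.6, delete the sentence on efficacy or restrict it to the per-protocol set.
2. In Section 2.10, state that all randomised participants stay in the FAS, in the arm to which they were randomised, whatever the reason for withdrawal. Make Sections 2.3.6 and 2.3.7 refer to that rule.
3. State that week-2 serum creatinine is sought from participants who have stopped study treatment, where they consent.
4. Align the adverse-reaction wording in Section 2.3.6 with the Section 2.10 safety set: everyone who took study drug, with or without a recorded reaction.
5. Clarify that reason (5) means ineligibility at baseline that is discovered later.

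The cost is small: protocol wording, plus some extra week-2 blood draws.

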### 2.4. Randomization and Blinding

A simple random method is adopted, and SPSS (version 21.0) software will be used by independent biostatisticians to generate random number sequences. Written informed consent should be signed immediately by himself/herself, agreeing to voluntarily enroll in the trial. Participants should be consented for randomization and participation. According to the sequence of enrolling in clinical observation, participants will be randomly numbered and divided into the RG group, the CHF group, and the RG + CHF group by investigators at 1 : 1 : 1 ratio. During randomization producer, sealed envelopes marked with sequential coding numbers will be adopted to keep allocation details, and group allocation should be kept blind to patients, biostatisticians, and investigators. As placebo is not used in the control group, it is not possible to be blind in the treatment. However, it is masked from staff performing all laboratory investigations.

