### 2.9. Sample Size Estimation

The sample size will be calculated according to the primary outcome of baseline Scr change. Based on previous studies and literature reports [26, 30], the mean value of Scr was 160.39 *μ*mol/l, and the standard deviation was 44.43 *μ*mol/l. We thus hypothesize that Scr for CHF combing RG group would be significantly lower than the other two groups by more than 30 *μ*mol/l. It is calculated using the sample size estimation software PASS (version 15.0.3) to achieve test efficacy 1–*β* = 0.90 and significant difference *α* = 0.05 (one-sided test). Considering 20% drop rate, the estimated sample size for randomization will be 54 cases in each group for a total of 162 cases.

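### Section 2.3.6 drops withdrawn participants from the efficacy analysis, while Sections 2.3.7 and 2.10 keep them in

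*Protocol article*

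**What the plan says.** Section 2.3.6 of the protocol article gives six withdrawal criteria: poor compliance, allergy to the study medicine, loss to follow-up ("cases lost to follow-up in the trial"), the participant's request, ineligibility discovered after inclusion, and sudden serious illness unrelated to acute kidney injury (AKI). Complications that reflect progression of AKI are expressly protected from simple exclusion. Of withdrawal cases it then says: "Those cases are not statistically analyzed for efficacy". Only their adverse reactions are kept. The section ends with a narrower rule: "Participants who withdraw within two weeks after treatment will be defined as missing case", and such participants are left out of the per-protocol population.

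Section 2.3.7 starts from "Natural shedding and loss of follow-up during observation may occur during the trial", also covers participants who leave because of severe complications, and concludes: "Shedding cases should be documented in detail, and intention-to-treat (ITT) analysis should be performed in the end".

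Section 2.10 states: "The principal analysis will be conducted on a full analysis set (FAS), which consists of participants randomly allocated". It defines a separate per-protocol population of compliant completers without major violations.

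Two other statements bear on the consequences. Section 2.4: "As placebo is not used in the control group, it is not possible to be blind in the treatment". Section 2.9: "Considering 20% drop rate, the estimated sample size for randomization will be 54 cases in each group".

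**The concern.** The article fixes two incompatible rules for the same people and gives neither precedence. An analyst could exclude withdrawn participants by citing 2.3.6 or keep them by citing 2.3.7 and 2.10, and could make that choice after seeing the data.

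If 2.3.6 is followed, exclusion from efficacy depends on events after randomisation, in a trial where patients and treating staff know the arm. Laboratory staff are masked and samples go to a central laboratory, so measurement of Scr is protected. The choice of who is analysed is not.

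The document gives reason to expect unequal exclusion. Section 2.12 mentions rash and other allergic symptoms for reduced glutathione (RG) and no obvious adverse events for Chuan Huang Fang (CHF), so the allergy criterion is more likely to remove participants from the two arms that contain RG. The arms also differ in burden (daily infusion; oral drug plus enema; both), so compliance may differ too.

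**Working it through.** **The rules side by side, for a randomised participant**

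| Situation | 2.3.6 (efficacy) | 2.3.7 | 2.10 (FAS) |
|---|---|---|---|
| Poor compliance | out | not named | in |
| Allergy to study medicine | out | not named | in |
| Lost to follow-up | out | in (ITT) | in |
| Own request | out | not named | in |
| Found ineligible after inclusion | out | not named | in |
| Serious complication unrelated to AKI | out | in (ITT) | in |
| Complication reflecting AKI progression | protected | in (ITT) | in |

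The first six rows conflict with 2.10, and two of them also conflict with 2.3.7. The last row does not conflict and is not part of this point.

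**Effect on the analysis sets.** Under 2.3.6, participants withdrawn for poor compliance and those who stop early leave every efficacy analysis. On compliance and completion, the FAS then largely collapses onto the per-protocol set that 2.10 defines separately.

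**Scale.** Inputs from Section 2.9: 54 per group, 162 in total, 20% drop rate, SD 44.43 μmol/l, target difference 30 μmol/l.

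- The planned size can be reproduced. A three-group ANOVA F-test with means 0, 0 and 30, SD 44.43, α = 0.05 and power 0.90 needs 42.6, so 43 per group; 43 / 0.80 = 53.75, so 54.
- Planned drop: 0.20 × 54 = 10.8 per group; 0.20 × 162 = 32.4 in total.

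**Illustration of the shift.** Suppose one arm leaves out k more participants with an available week-2 Scr than its comparator, and the mean Scr of those left out is d above that of those kept. An arm's full mean exceeds its kept mean by (number left out) × d / 54, so the between-arm difference shifts by k × d / 54. Both k and d are assumptions.

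| k | d = 44.43 (one SD) | d = 22.215 (half SD) |
|---|---|---|
| 1 | 0.82 μmol/l (2.7% of 30) | 0.41 (1.4%) |
| 3 | 2.47 (8.2%) | 1.23 (4.1%) |
| 5 | 4.11 (13.7%) | 2.06 (6.9%) |

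If those left out have higher Scr, the arm that loses more of them looks better than it is.

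**Limit of the illustration.** Table 3 schedules Scr at baseline and week 2 only. Section 2.5 speaks of weekly examinations but refers to Table 3 for the time points. A participant lost before week 2 therefore has no scheduled post-baseline Scr. The formula does not apply to that participant, and the label matters only through the missing-data method.

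**The case against.** The best defence is that 2.10 is the statistical section and governs the principal analysis, while 2.3.6 deals with participant handling and means only exclusion from the per-protocol set, which its last sentence names. That may be what was intended, but the text does not say so. The efficacy exclusion carries no limit, and the per-protocol rule is a separate, narrower sentence. The warning against simply excluding AKI-related complications from efficacy makes sense only if withdrawal otherwise means such exclusion.

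Several narrower objections have weight:

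- The FAS and per-protocol set would not be identical. A participant can fall short of good compliance without being withdrawn.
- RG allergy is described as occasional, and people with known allergy are excluded at entry. Both the RG and RG + CHF arms receive RG, so this route bears on comparisons with CHF alone and gives no evident imbalance between RG + CHF and RG.
- The shift is modest against sampling error. The standard error of a pairwise difference is 44.43 × √(2/54) = 8.6 μmol/l, so the largest illustrated shift is about half of it. With 43 rather than 54 observed per arm, the one-SD range becomes 1.0 to 5.2 μmol/l.
- Leaving participants who were never eligible out of a FAS can be defended. Section 2.10 makes no such exception, and one would not settle the other withdrawal reasons.

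These points limit the likely bias. They do not remove the contradiction.

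**Conclusion.** The concern holds. Sections 2.3.6, 2.3.7 and 2.10 cannot all be followed for the same randomised participant, and the conflict concerns the analysis population for the primary outcome. It is not a detail left to a statistical analysis plan, because the article states both rules. Confidence in the textual conflict is high.

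The size of any bias is unknown. The illustrated 0.4 to 4.1 μmol/l rests on an assumed excess of one to five exclusions, an assumed difference of half to one SD, and an available week-2 Scr for those left out. The document does not say how many of the roughly 11 per arm in the planned drop would have that value. The point should be corrected before data are seen.

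**What to change.** - In 2.3.6, delete the exclusion of withdrawal cases from efficacy or restrict it to the per-protocol set.
- State that all randomised participants remain in the FAS/ITT efficacy analysis, whether they are labelled withdrawn or shed.
- Collect and use the already scheduled week-2 Scr from participants who stop treatment, for example for poor compliance or allergy, but agree to stay in follow-up.
- Leave the handling of a missing week-2 Scr to the statistical analysis plan.

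Listing loss to follow-up in only one of 2.3.6 and 2.3.7 would be tidier, but is editorial once the analysis rule is clear.

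The cost is a wording amendment to 2.3.6 and 2.3.7 and slightly more follow-up at the existing week-2 visit. No new visit and no change in sample size are needed.
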